## Abstract

**Background:**

Bronchiectasis unrelated to cystic fibrosis (CF) is being increasingly recognized in children and adults globally, both in resource-poor and in affluent countries. However, high-quality evidence to inform management is scarce. Oral amoxycillin-clavulanate is often the first antibiotic chosen for non-severe respiratory exacerbations, because of the antibiotic-susceptibility patterns detected in the respiratory pathogens commonly associated with bronchiectasis. Azithromycin has a prolonged half-life, and with its unique anti-bacterial, immunomodulatory, and anti-inflammatory properties, presents an attractive alternative. Our proposed study will test the hypothesis that oral azithromycin is non-inferior (within a 20% margin) to amoxycillin-clavulanate at achieving resolution of non-severe respiratory exacerbations by day 21 of treatment in children with non-CF bronchiectasis.

**Methods:**

This will be a multicenter, randomized, double-blind, double-dummy, placebo-controlled, parallel group trial involving six Australian and New Zealand centers. In total, 170 eligible children will be stratified by site and bronchiectasis etiology, and randomized (allocation concealed) to receive: 1) azithromycin (5 mg/kg daily) with placebo amoxycillin-clavulanate or 2) amoxycillin-clavulanate (22.5 mg/kg twice daily) with placebo azithromycin for 21 days as treatment for non-severe respiratory exacerbations. Clinical data and a parent-proxy cough-specific quality of life (PC-QOL) score will be obtained at baseline, at the start and resolution of exacerbations, and on day 21. In most children, blood and deep-nasal swabs will also be collected at the same time points. The primary outcome is the proportion of children whose exacerbations have resolved at day 21. The main secondary outcome is the PC-QOL score. Other outcomes are: time to next exacerbation; requirement for hospitalization; duration of exacerbation, and spirometry data. Descriptive viral and bacteriological data from nasal samples and blood inflammatory markers will be reported where available.

**Discussion:**

Currently, there are no published randomized controlled trials (RCT) to underpin effective, evidence-based management of acute respiratory exacerbations in children with non-CF bronchiectasis. To help address this information gap, we are conducting two RCTs. The first (bronchiectasis exacerbation study; BEST-1) evaluates the efficacy of azithromycin and amoxycillin-clavulanate compared with placebo, and the second RCT (BEST-2), described here, is designed to determine if azithromycin is non-inferior to amoxycillin-clavulanate in achieving symptom resolution by day 21 of treatment in children with acute respiratory exacerbations.

**Trial registration:**

Australia and New Zealand Clinical Trials Register (ANZCTR) number http://ACTRN12612000010897. http://www.anzctr.org.au/trial_view.aspx?id=347879

## Background

Bronchiectasis unrelated to cystic fibrosis (CF) is an heterogenous condition with many initiating events. It is now considered more common than thought previously, especially in developing countries [1], in socioeconomically disadvantaged Indigenous communities in affluent countries [2] and as a co-morbidity of other chronic pulmonary diseases, such as asthma [3,4] and chronic obstructive pulmonary disease (COPD) [5]. Bronchiectasis affects all age groups, including infants [6]. Although the consequences of bronchiectasis are predominantly related to respiratory morbidity, there are also independent cardiovascular effects, such as coronary artery disease [7,8], which are likely to worsen with the systemic inflammation arising from chronic pulmonary infection.

Over the past 15 to 20 years, it has been increasingly recognized that non-CF bronchiectasis is a major contributor to chronic respiratory morbidity [9,10] and mortality [11,12] worldwide [2,13]. In our recently completed multicenter study of 346 Australian children newly referred for chronic cough and managed using a standardized protocol [14], 31 (9%) had radiologically proven bronchiectasis [15]. In the USA, the average number of bronchiectasis-associated hospitalizations increased by 2 to 3% per year between 1993 and 2006, and during this period, the average age-adjusted annual hospitalization rate was 16.5 per 100,000 of the population [9]. In some populations from affluent countries, the prevalence of bronchiectasis is one of the highest reported in the world, such as in Central Australia, where 1 in 68 Indigenous children are affected [16]. Similarly, in New Zealand, the estimated national prevalence rates of bronchiectasis are much higher in Maori (1 in 2300) and Pacific Island (1 in 625) children than in New Zealand European (1 in 7440) children aged under 15 years [17]. The minimum national incidence of non-CF bronchiectasis before the age of 15 years is 1 in 1,700 births, compared with 1 in 3,179 births for a diagnosis of CF in New Zealand [17]. In the European Union and the USA, the prevalence of CF is 7.4 to 7.9 per 100,000 (whole population data) [18]. Indeed, there are far more patients with bronchiectasis than patients with CF attending respiratory services globally [19]. In the US, about 30,000 [20] people have CF, whereas over 110,000 people have non-CF bronchiectasis [13]. Moreover, the latter is likely to be an underestimate, as many cases of non-CF bronchiectasis are misdiagnosed. or co-exist with asthma [3,4,18] and COPD [5].

Effective clinical management reduces both short-term and long-term morbidity (and probably mortality) associated with bronchiectasis [1,21-23]. Cohort data have shown that about 80% of newly diagnosed adults (non-smokers) with bronchiectasis reported symptoms dating back to childhood, and that the duration of chronic cough (the most common symptom of bronchiectasis [24]) was related (r = −0.51, *P*<0.001 in non-smokers) to lung function at diagnosis [25]. Arguably, appropriate overall management and treatment of exacerbations (leading to a reduction in persistent symptoms) potentially prevents or reduces deterioration of chronic respiratory disease [26]. Our study and a London-based retrospective study both found that with appropriate treatment in specialized centers, lung function improves and can be maintained [22,23]. However, despite substantial improvements, those with poor lung function at diagnosis were still likely to have poor lung function 5 years later [23]. We also found that the only significant predictor of decline in forced expiratory volume in 1 second (FEV_1_) was the frequency of hospitalized exacerbations, and that FEV_1_ percentage predicted declined by 1.95% with each hospitalized exacerbation [23]. In addition to the biologic effects of respiratory exacerbations, these episodes also impair quality of life (QOL) and well-being. as shown by deteriorating scores for QOL and on the Depression, Anxiety and Stress Scale (DASS) during exacerbations [27]. Taken together, as airway injury in children is superimposed upon the physiological changes involving lung growth and development [28,29], we speculate that early and effective management of bronchiectasis exacerbations in children may lead to reduced hospitalizations, better QOL, and improved future adult lung function.

Although most respiratory physicians will treat acute exacerbations intensively with antibiotics and airway clearance [24,30], some exacerbations are caused by viral infections, and may not require antibiotic therapy. However, it is possible that viral-bacterial interactions in the airways could promote or prolong endobronchial bacterial infection, which, with the accompanying inflammatory cascade, is a risk for additional lung injury [26,31]. To address whether antibiotics are superior to placebo at providing short-term clinical benefits, the first component of our Bronchiectasis Exacerbation Study (BEST), is a multicenter randomized controlled trial (RCT; BEST-1) designed to answer the question: ‘Does azithromycin or amoxycillin-clavulanate, compared with placebo, improve the resolution of respiratory exacerbations on day 14 of treatment?’ [32].

The second component of BEST (BEST-2) seeks to determine whether the two antibiotics used in BEST-1 are equivalent at achieving resolution of an acute respiratory exacerbation in children with bronchiectasis, compared with placebo. Based on available, but limited, data on the microbiology of lower-airway secretions in children with non-CF bronchiectasis [33], amoxycillin-clavulanate is currently recommended as the first-line empirical oral-antibiotic treatment for non-severe bronchiectasis exacerbations in children [24]. However, amoxycillin-clavulanate requires dosing two to three times per day, and causes gastrointestinal symptoms in many children. Oral azithromycin is attractive as an alternative first-line therapy because of its long half-life, markedly reduced dosing schedule, and good safety profile in children [34]. Although azithromycin can be used 3 days/week [35] or even once weekly [36], our proposed study uses a daily dose in order to maintain effective blinding of the medications. However, if daily azithromycin is shown to be equivalent to amoxicillin-clavulanate, then extended-interval azithromycin dosage schedules could be trialed in appropriate clinical settings where reduced dosing frequency is particularly appealing, such as for patients likely to have poor adherence.

As well as having anti-bacterial activity against most respiratory bacterial pathogens associated with non-CF bronchiectasis [37], azithromycin has additional anti-microbial properties that could prove beneficial. These include its unique bactericidal activity against intracellular strains of non-typeable *Haemophilus influenzae*[38], inhibitory effects upon biofilm formation [39], and anti-viral properties [40]. Furthermore, as a member of the macrolide class of antibiotics, it also has immunomodulatory and anti-inflammatory functions [41]. Given the emerging importance of both airway inflammation and biofilm development in the pathogenesis of acute and chronic respiratory disease [26,42], azithromycin may be a valuable intervention. Nevertheless, no RCTs have yet been carried out for azithromycin to help determine its role in treating acute exacerbations of bronchiectasis. Despite the lack of high-level evidence, azithromycin is sometimes used to treat adults with bronchiectasis exacerbations, perhaps as an extension of its reported positive effects on acute exacerbations of COPD [43]. By contrast, two RCTs of maintenance azithromycin therapy have been conducted in adults with non-CF bronchiectasis. One was a small, non-blinded, double cross-over RCT, where 6 months of azithromycin therapy was shown to improve lung function and reduce exacerbation frequency [44]. More recently, a 6-month, parallel, double-blind, placebo-controlled trial in New Zealand adults with bronchiectasis reported that azithromycin decreased exacerbation events, but did not alter lung function or QOL measures [45].

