### Intervention and follow-up

A double-dummy design is planned. If eligibility is fulfilled, and after informed consent has been obtained, the child will be randomized to one of two arms. At the start of the exacerbation, the child will receive orally: 1) azithromycin with placebo amoxycillin-clavulanate or 2) amoxycillin-clavulanate with placebo azithromycin. The azithromycin dose is 5 mg/kg/day (to a maximum of 200 mg daily, and for amoxycillin-clavulanate it is 22.5 mg/kg/dose twice daily (maximum 900 mg/dose). Equivalent volumes of placebo will be given for both trial medications. All treatments will continue for 21 days.

An exacerbation is defined as an increase in sputum volume or purulence, or change in cough (>20% increase in cough score [46] or type (dry to wet) [47]) for more than 3 days. We validated this definition in our prospective study, and found that the kappa values (between clinicians) of these symptoms and signs were excellent (>0.75) [48]. Daily diaries will also be collected during exacerbations until the scores for 2 or more days reflect the child’s baseline state, which for each child will be established at enrolment, prior to any exacerbations. This assessment consists of a combination of symptoms (daily cough (yes/no), cough quality (wet/dry/none), cough score [46] averaged over two consecutive days) and signs (sputum color (if any present) using a color chart card (BronkoTest Ltd, London, UK), and crackles on chest auscultation). Children will be reviewed on days 14 and 21, and at resolution of the exacerbation. The exacerbation is considered resolved when symptoms and signs are the same as the baseline state. Post-exacerbation, the children will be followed up and evaluated clinically every 3 months for a period of 18 months or until their next exacerbation (whichever is sooner). The time to next exacerbation will be determined by duration of days from the resolution of the current exacerbation to the beginning of the next exacerbation.

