### Sample size

We plan to enroll 170 children (85 per arm), providing 90% power (α = 0.05, 1-sided) with 20% non-inferiority margin to detect 80% resolution rate by day 21. The margin selected is relatively large in statistical terms, but the physicians considered it clinically appropriate. As the primary outcome will be obtained in all enrolled children, retention fraction has not been factored in for the intention-to-treat analysis.

The main secondary outcome (secondary aim 1) is PC-QOL. Based on a non-inferiority limit of 0.9 (minimum important difference [57]) and standard deviation of 0.9, our sample size provides a power of 99.9% (α = 0.05, one-sided 95% CI) for data from at least 136 children (assuming at least 80% retention of children enrolled). For secondary aim 2 (see list under ‘Aims of the study’), we will be examining eight main factors, and thus a sample size of 136 exceeds the recommended minimum (n = 10 per factor) [65]. The eight factors are: smoking, age, underlying etiology, detection of virus (any versus none, then single versus multiple viruses), presence of azithromycin resistance, and levels of various blood markers (IL-6, IL-10, IP-10).

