The 20% margin used for our study, although relatively large, was deemed clinically appropriate, given the potential major advantage of future once-weekly dosing with azithromycin compared with twice-daily dosing wit amoxycillin-clavulanate. In disadvantaged communities, adult-supervised twice-daily dosing is not always possible, and may result in children with exacerbations receiving suboptimal treatment. By contrast, once-weekly dosing is feasible with weekly home or clinic visits; we have achieved this outcome in studies involving remote Indigenous settings in Australia [50] and in New Zealand [78]. Thus, if non-inferiority between amoxycillin-clavulanate and azithromycin is established, this would provide an easier option for managing exacerbations, and could substantially improve adherence in disadvantaged settings.

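### The 20-point margin is not tied to any known effect of amoxycillin-clavulanate over placebo, so the treatment conclusion drawn from non-inferiority should be made conditional on BEST-1

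*Protocol article*

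**What the plan says.** **Design.** The arms, under Intervention and follow-up, are "1) azithromycin with placebo amoxycillin-clavulanate or 2) amoxycillin-clavulanate with placebo azithromycin". Placebo is present only as the dummy for the other drug. The aims, the hypothesis and the primary analysis all concern azithromycin against amoxycillin-clavulanate. Two places read differently: the Background says BEST-2 asks whether the antibiotics "are equivalent at achieving resolution of an acute respiratory exacerbation in children with bronchiectasis, compared with placebo", and the Methods paragraph of the abstract calls the study a "randomized, double-blind, double-dummy, placebo-controlled, parallel group trial".

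**What is known of the comparator.** The abstract states that "there are no published randomized controlled trials (RCT) to underpin effective, evidence-based management of acute respiratory exacerbations in children with non-CF bronchiectasis", and the main Discussion repeats this. The Background notes that "some exacerbations are caused by viral infections, and may not require antibiotic therapy" and gives the comparison of each antibiotic with placebo, at day 14, to BEST-1.

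**The margin.** Sample size says: "The margin selected is relatively large in statistical terms, but the physicians considered it clinically appropriate". The Discussion adds the prospect of a less frequent azithromycin schedule and better adherence in disadvantaged settings. Neither place cites an effect of amoxycillin-clavulanate over placebo.

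**The conclusion.** The Discussion says that "if non-inferiority between amoxycillin-clavulanate and azithromycin is established, this would provide an easier option for managing exacerbations". The Conclusion section expects simpler management and input to treatment guidelines. Neither statement depends on what BEST-1 finds.

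**The concern.** A non-inferiority trial without a placebo arm shows that the test drug works only by an indirect step: the comparator must be known to beat placebo, and by enough that losing the whole margin still leaves a worthwhile benefit. Here the article itself says the first part is unknown. If amoxycillin-clavulanate improves resolution by less than 20 points, a drug with no effect lies inside the margin and can be declared non-inferior.

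At stake is the reading of a positive primary result. From BEST-2 alone, 'both antibiotics work' and 'neither does more than placebo' fit that result equally well. The two trials' primary results do not line up directly either, because BEST-1 judges resolution at day 14 and BEST-2 at day 21.

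**Working it through.** **Inputs (Sample size section).** 85 per arm; 80% resolution, taken as equal in both arms; 20% margin; 90% power; alpha 0.05 one-sided; no allowance for dropout.

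**Step 1: reproduce the sample size.** With an absolute margin of 0.20 and equal rates,

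n per arm = (z₁₋α + z₀.₉₀)² × [0.8×0.2 + 0.8×0.2] / 0.20² = (z₁₋α + 1.282)² × 8.

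- One-sided 0.025: (1.960 + 1.282)² × 8 = 84.06, so 85 per arm and 170 in total. This matches.
- One-sided 0.05 as printed: (1.645 + 1.282)² × 8 = 68.5, so 69 per arm and 138 in total. At this alpha, 85 per arm would have 94.7% power.

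The match supports reading the margin as 20 absolute points: from 80% resolution down to 60%, or non-resolution from 20% to 40%. The printed alpha does not give the printed size. That is a separate matter, so both alphas are carried below.

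**Step 2: chance of declaring non-inferiority if azithromycin is no better than placebo.** The documents give no placebo resolution rate, so it is assumed over a range. Let p_C = 0.80 and p_T = the assumed placebo rate:

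SE = √{[0.80×0.20 + p_T(1 − p_T)] / 85}

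P(non-inferior) = Φ[(p_T − 0.80 + 0.20)/SE − z₁₋α]

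Worked case, p_T = 0.70: SE = √[(0.16 + 0.21)/85] = 0.0660; 0.10/0.0660 = 1.516; Φ(1.516 − 1.645) = 0.449; Φ(1.516 − 1.960) = 0.328.

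| Assumed placebo rate | Comparator effect | SE | One-sided 0.05: normal / exact binomial | One-sided 0.025: normal / exact binomial |
|---|---|---|---|---|
| 60% | 20 points | 0.0686 | 5.0% / 5.1% | 2.5% / 2.5% |
| 65% | 15 points | 0.0675 | 18.3% / 18.4% | 11.1% / 11.4% |
| 70% | 10 points | 0.0660 | 44.9% / 44.9% | 32.8% / 33.5% |
| 75% | 5 points | 0.0639 | 75.8% / 76.0% | 65.0% / 65.6% |
| 80% | 0 points | 0.0614 | 94.7% / 94.8% | 90.3% / 90.3% |

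The exact column sums binomial probabilities over all outcomes, using the Wald lower limit.

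**Step 3: read the table.** The chance that a drug equal to placebo passes is held to the nominal level only if the comparator's true effect is at least 20 points. At a 10-point effect it is 33% to 45%, depending on alpha and method. No statement in the article places the effect above 20 points.

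**The case against.** The strongest reply is that BEST-2 does not set out to show efficacy over placebo. The article describes two trials: BEST-1 tests each antibiotic against placebo, and BEST-2 compares the antibiotics with each other. Amoxycillin-clavulanate is the currently recommended first-line oral treatment, so calling azithromycin an easier option can be read as a statement relative to standard care. The margin also has a stated rationale beyond physician opinion, namely feasibility and adherence. This stands in part. It makes the design legitimate, but it does not supply the missing condition in the Discussion and Conclusion, and a convenience argument does not show how much effect there is to give up.

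Three stronger readings are tempting, and the documents do not support them.

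- A reader might infer that the protocol plans to judge the antibiotics against placebo and has no arm to do so. The clause occurs once, in the Background. Hypothesis, aims, design and analysis all state non-inferiority to amoxycillin-clavulanate, and nothing planned depends on the clause.
- A reader might take the table as an inflated error rate of the planned test. It is not. At any placebo rate above 60%, the true difference is within 20 points and a non-inferiority finding is correct for the stated hypothesis. The figures show the limit of the inference.
- A reader might conclude that azithromycin's efficacy can never be established. That is true only of BEST-2 taken alone; BEST-1 may supply the evidence.

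It can also be said that a day-14 outcome adds little, because duration of exacerbation is already a secondary outcome and Kaplan-Meier curves of time to resolution are planned. Day-14 resolution could be read from those curves, but naming it in advance removes any choice after the results are seen. The different time points are themselves explained in the section on outcome measures and timeframe.

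**Conclusion.** The point holds as a limit on what BEST-2 can conclude, not as a fault in its hypothesis, arms or test. With the comparator's effect unknown in the documents and the margin set on other grounds, non-inferiority shows only that azithromycin is not worse than amoxycillin-clavulanate by more than 20 points.

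The size depends on an assumed quantity. Given 80% resolution on the comparator and 85 per arm, an azithromycin arm equal to placebo would pass about 5% of the time at one-sided 0.05 if the comparator's effect were 20 points, and 76% of the time if it were 5 points. If the effect were known to be well above 20 points, the concern would fall away. This should be fixed, but it is not a reason to hold the trial. The placebo wording is a minor correction.

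**What to change.** 1. **Discussion and Conclusion.** State that non-inferiority supports azithromycin as an effective treatment only if BEST-1 shows amoxycillin-clavulanate superior to placebo by an amount that makes a 20-point loss acceptable. Otherwise, conclude only that azithromycin was not worse than amoxycillin-clavulanate by more than 20 points.
2. **Secondary outcomes.** Name resolution by day 14. The visit exists already: "Children will be reviewed on days 14 and 21, and at resolution of the exacerbation". This lines up with the BEST-1 time point. Label any comparison with the BEST-1 placebo arm as non-randomised and supportive, note that BEST-1 children may re-enter BEST-2, and say that a day-14 effect is only indirect evidence for a day-21 margin. The BEST-1 protocol is not shown, so check that both trials define resolution alike.
3. **Wording.** In the Background, delete the comparison with placebo and replace 'equivalent' with 'non-inferior'. In the abstract, describe the trial as active-controlled with double-dummy placebo.

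The cost is wording and one tabulation from a visit already scheduled. Arms, sample size, margin and primary analysis stay as they are. The drawback is a more cautious conclusion if BEST-1 shows a small effect. The change should be made before results are known, so that the condition cannot look chosen to suit them.
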